## Abstract

Introduction: Obesity and overweight are significant health problems among Australian children. Parents play a vital role in establishing healthy eating behaviors in their children. However, parents often experience difficulties in implementing effective parenting practices and lack confidence in their ability to help children adopt these behaviors. This trial will evaluate the efficacy of an online program, Healthy Habits Triple P, in improving children’s snacking and mealtime behaviors and related parenting practices. Methods and analysis: This is a single-blinded, randomized controlled trial for parents of young Australian children aged 2–6 years. Participants will be recruited through childcare centers, social media, online parent forums and existing networks. The participants in the intervention arm will receive access to a web-based parenting intervention in addition to nutrition-related information for parents published by the National Health and Medical Research Council of Australia; those in the control arm will receive nutrition-related information only. After the completion of the study, the parenting intervention will be offered to the control arm. The primary outcome will be improvement in children’s eating habits. The secondary outcomes include parents’ self-efficacy, confidence, children’s mealtime behaviors and mealtime parenting strategies. Both primary and secondary outcomes will be evaluated through online-administered, validated parent-reported questionnaires. We will also undertake a quantitative and qualitative evaluation of the practicality and acceptability of the intervention.

## 1. Introduction

The prevalence of *overweight* and *obesity* has risen from 4% in 1975 to 18% in 2016 among children and adolescents across the world [1]. Around 25% of Australian children and adolescents are currently overweight or obese, leading to worse health outcomes and poorer wellbeing [2]. Hayes et al. (2016) found that the direct healthcare costs of children with obesity aged 2–4 years was 1.62 times higher than healthy weight children [3]. The longer-term burden of disease from overweight and obesity is even greater, as it is a driver for multiple diseases including diabetes, musculoskeletal conditions, cardiovascular disease, kidney disease, asthma, dementia and various cancers in later life [4].

A complex interaction of biological, environmental and social factors influences the likelihood of a child gaining excess weight, such as differences in appetite and metabolism, accessibility of healthy food options and avenues for safe outdoor play [5,6]. Although the causes are complex, intake of energy-dense, nutrient-poor foods is a key contributor to obesity in Australian school children [7]. National guidelines recommend that children regularly consume a variety of fruits and vegetables, limit intake of treat and fast foods, consume water as the main drink and eat meals together with their family at the table [8,9]. Specific guidelines recommend that children consume a minimum of 1–2 servings of fruit and 2–3 servings of vegetables per day; however only 6% of children aged 5–14 years met these recommendations in 2017–2018 and almost half (45%) of the children aged 2–17 years regularly consumed sugar-sweetened food and/or diet drinks [10]. Among 2–3 year-old Australian children, discretionary food items (foods high in energy with saturated fat or added sugars or added salt) accounted for 29% and 32% of total energy intake/day for boys and girls, respectively [11]. Thirty-one percent of children are also likely to consume sugar-sweetened drinks on one to three days a week [11].

Parenting, parental role modelling and the home environment are important modifiable determinants of healthy eating in children [12,13]. Evidence from an observational study also demonstrated a cumulative model of association between family mealtime behaviors and child obesity status [14]. In this study, cumulative risk factors, such as family mealtime routines pertaining to regularity, roles and flexibility; and mealtime interactions pertaining to positive communication accounted for 12% of the variance in children’s body mass index [14]. The current study is framed around the importance of positive parenting practices that are proximal to establishing positive mealtime behaviors and communication.

The early years of life are also when children develop values, beliefs and attitudes, and adopt practices related to food intake [15]. Importantly, healthy practices adopted in childhood are more likely to continue into adolescence and adulthood [16].

A recent national survey conducted by the Royal Children’s Hospital Melbourne identified unhealthy diet as a top child health concern among Australian parents [17], yet many Australian children do not adhere to the recommended behavioural practices [18], as outlined in the national guidelines [8,9]. Within the family environment, both general and diet-specific parenting practices are related to children’s eating and mealtime behaviours [19]. General parenting styles are higher-order constructs, whereas parenting practices are more proximal in determining child behaviour [20]. For example, an authoritative parenting style is linked to a healthier weight and dietary outcomes in children, as compared to authoritarian, permissive or neglectful parenting styles [21]. Specific parenting practices, such as the types of food that parents make available to their children and parental role modelling, will tend to have a more direct effect on children’s eating behaviours [22].

A recent systematic review by Gomes et al. (2021) found that, despite a growing body of research examining the effects of parent-focused web-based interventions to promote children’s healthy diet, there is a paucity of studies examining the effects on parental feeding practices [23]. There is emerging evidence of web-based interventions improving parents’ knowledge, behaviour and attitudes in the context of child obesity and overweight [24,25]. Although most of the web-based interventions were theory-driven and included standard behaviour change techniques (e.g., instruction and demonstration of parenting behaviours) [26,27], few included strategies, such as the identification of oneself as a role model [28], promotion of children’s self-regulation or the management of parents’ emotional responses to children’s eating challenges, all of which are important to the development of healthy eating behaviours in childhood [29].

As a public health priority, government agencies recommend using primary and secondary prevention strategies to minimize the burden of diseases and associated risk factors [30]; however, despite these recommendations, a majority of parenting interventions for childhood obesity and overweight are treatment-based rather than prevention-oriented [25]. The Triple P (Positive Parenting Program) is a multi-level, prevention-oriented program, based on social learning principles and grounded in a self-regulatory framework, that takes a minimal sufficiency approach to support the development of parent and child self-regulation [31]. It aims to enhance parents’ knowledge, skills and confidence; promotes positive and nurturing environments; teaches strategies to support healthy child development and manage children’s problem behaviours; and supports parents with self-care and managing their own stress [32]. All of these factors have been identified as important to the development of healthy eating and mealtime behaviours in childhood [23]. The aim of this trial is to examine the efficacy of a prevention-based online intervention (Healthy Habits Triple P) designed to support parents to develop healthy eating and mealtime behaviours with their young children (2–6 years) in Australia.

## 2. Methods and Analysis

This protocol is reported in accordance with the guidelines presented in the SPIRIT 2013 statement for protocols of clinical trials [33].

### 2.1. Design

The proposed study is a randomized controlled trial to assess the efficacy of a web-based parenting support program for promoting healthy eating and mealtime behaviours. There will be two data collection time-points: baseline and post-intervention (6 weeks after the intervention). All participants in the intervention group will receive the web-based Healthy Habits Triple P intervention. The control group, on the other hand, will only have access to the online intervention after completing the six-week follow-up assessment. All parents will receive a brochure on child nutrition, produced by the Australian government (National Health and Medical Research Council (2021)) [34].

### 2.2. Participants and Setting

Any parent/caregiver interested in taking part in the program, living in Australia, and with at least one child in the 2–6 years age group is eligible to participate. Parents/caregivers will be included if they are able to read and understand English and have access to an internet-enabled device. Only one parent and child per family will be eligible to participate. For families with multiple children in the target age range, parents will be asked to nominate the child whose eating and mealtime habits they are most concerned about; otherwise, they will be asked to select their youngest child. Exclusion criteria are: (1) a child with a disability; (2) a child with behavioural difficulties requiring parents to seek professional help; and (3) parents currently receiving psychological support or counselling.

### 2.3. Sample Size

In this trial, following the recommendations of Whitehead et al. (2016), a sample size of 15 families per arm will be required with 90% power and two-sided 5% significance [35] and medium effect size (Cohen’s d = 0.5) based on meta-analysis of the effects of the Triple P on parenting and child outcomes [36]. Allowing for an attrition rate of 60%, 25 participants will be recruited to each arm. We have allowed for an attrition rate of 60%, which is greater than the traditional 20% attrition rate commonly used in trials of public health interventions. Participant anonymity in this study may contribute to reduced rates of assessment completion post-intervention [37]. An increase in sample size by 60% will ensure that sufficient sample size is retained.

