### 2.5. Randomisation, Allocation and Blinding

After the baseline survey is completed, participants will be randomly allocated to the intervention or the control groups in a 1:1 ratio using computer-generated block randomization schedule by a researcher not involved in data collection or recruitment, to facilitate equal group allocation. Because of the type of intervention used in this trial, participants cannot be blinded to group allocation.

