### 2.11. Quantitative Data Analysis

Quantitative data from this pilot study will be descriptive, with outcomes being interval estimates of variables relating to children’s dietary habits, parenting and child behaviours and parenting efficacy. Data will be de-identified, and SPSS (Version 27.0. Armonk, NY, USA: IBM Corp) will be used to conduct data analysis. Data will be examined for outliers and missing values. All data will be analyzed based on the intention to treat (ITT) principle. To account for repeated measurements, two-way repeated-measures ANOVAs will be used to evaluate changes in diet and other study outcomes between the intervention and control groups.

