The systematic review by Gomes et al. (2020) also found that most parent-focused web-based interventions did not improve diet-related parenting practices, except for food availability [23]. These negligible effects could be attributed to the inclusion of active control groups which, in many studies, received content that was overly similar to that provided to the intervention groups. In our trial, a waitlist control group will be used to maximize treatment separation and help prevent the problem of diluted effect, reported in previous studies.

It is important for parent-focused interventions: to acknowledge that each child has different choices and behaviours related to eating; to address parents’ own beliefs, attitudes and goals related to healthy eating; and to promote strategies to address other family factors, such as involving other caregivers [56]. Our intervention tailors to individual circumstances by helping parents to have realistic expectations of their child and themselves, given their child’s age and stage of development; to develop child-focused goals that are based on their own individual needs and priorities; and to develop and maintain effective daily routines by planning ahead and involving other family members.

One potential limitation of the study is the reliance on parent-reported measures for outcome assessment. However, at minimum, the results from this study will provide a good indication of whether an intervention such as this is practical to deliver and acceptable to parents. Future studies should explore the concordance of parent-reported parenting and child behaviour outcomes with observed measures of parent and child behaviour. This study provides the opportunity to estimate important study-specific parameters required to inform the design of future definitive controlled trials [57] which, if successful, will pave the way toward implementation as a preventive public health intervention within existing healthcare settings.

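### Section 2.3 attaches 90% power for d = 0.5 to 15 families per arm; a two-sample comparison of that size has about 26%, and the planned analysis reaches 90% only at a baseline-to-follow-up correlation of about 0.92, which is not stated

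*Protocol article*

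**What the plan says.** Section 2.3 (Sample Size) opens by referring to this trial and cites a published recommendation. It then states that "a sample size of 15 families per arm will be required with 90% power and two-sided 5% significance", with a "medium effect size (Cohen’s d = 0.5" taken from a meta-analysis of the parent programme. Sample size, power, significance level and effect size stand together in one sentence, in the form of an ordinary power statement. Section 2.5 fixes the comparison: "participants will be randomly allocated to the intervention or the control groups in a 1:1 ratio".

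Section 2.11 plans two-way repeated-measures ANOVA to compare change between the arms. Section 2.1 gives two assessment times. No correlation between baseline and follow-up is given.

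The purpose of the trial is described in two ways. The Abstract, the end of the Introduction, section 2.1 and the opening of the Discussion present an efficacy trial. Section 2.11 says "Quantitative data from this pilot study will be descriptive", and the last paragraph of the Discussion says that the study can "estimate important study-specific parameters required to inform the design of future definitive controlled trials".

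**The concern.** Fifteen per arm is far below what is usually needed to detect half a standard deviation with 90% power at two-sided 5%. If the figure is wrong, the article credits this trial with a 10% chance of missing a medium effect when the true chance is several times higher. A reader who relied on section 2.3 could then take a non-significant between-group result as fair evidence against the programme. The same misreading could affect the decision on any later definitive trial.

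**Working it through.** **Inputs.** From section 2.3: n = 15 per arm, power 90%, two-sided alpha 5%, d = 0.5. From section 2.5: 1:1 allocation. From sections 2.1 and 2.11: two time points and repeated-measures ANOVA. The baseline-to-follow-up correlation r is not stated, so it is varied below as an assumption.

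**Step 1: try to reproduce 15 per arm.** By the normal approximation, n per arm = 2(1.960 + 1.282)² / 0.5² = 84.1, rounded up to 85. The noncentral t gives 85.03, rounded up to 86. The stated 15 is not reproduced. Other standard choices do not reproduce it either:

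| Variant, d = 0.5 (t-test) | n needed |
|---|---|
| Two-sided 5%, 90% power | 86 per arm |
| One-sided 5%, 90% power | 70 per arm |
| Two-sided 5%, 80% power | 64 per arm |
| One-sample or paired, two-sided 5%, 90% power | 44 |

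**Step 2: power at the stated size.** The noncentrality is d√(n/2) = 0.5 × √7.5 = 1.369. The normal approximation gives Φ(1.369 − 1.960) = Φ(−0.591) = 27.7%. The noncentral t on 28 degrees of freedom gives 26.2%. The chance of missing d = 0.5 is therefore about 74%, against the 10% implied. If all 25 recruited per arm were retained, power would be 41.0%. With 15 per arm, 90% power is reached for d = 1.23.

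**Step 3: the planned analysis.** With two time points, the group-by-time test is a comparison of change scores. If d is expressed on the raw SD, the change score has SD √(2(1 − r)), so the effective standardised difference is 0.5 / √(2(1 − r)). The ANCOVA figures use 0.5 / √(1 − r²) and are shown only for comparison, since ANCOVA is not the planned analysis.

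| Assumed r | Change score, 15 per arm | ANCOVA, 15 per arm |
|---|---|---|
| 0 | 15% | 26% |
| 0.3 | 20% | 28% |
| 0.5 | 26% | 33% |
| 0.7 | 40% | 46% |
| 0.8 | 55% | 60% |
| 0.9 | 84% | 86% |

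The change-score analysis reaches 90% when 0.5 / √(2(1 − r)) = 1.226, that is r = 1 − (0.5/1.226)²/2 = 0.917. ANCOVA needs √(1 − (0.5/1.226)²) = 0.913. If d = 0.5 were instead meant on the change-score SD, power would be 26% whatever r is.

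**Step 4: precision at 15 per arm.** For a comparison of follow-up means, the 95% half-width is t(0.975; 28) × √(2/15) = 2.048 × 0.365 = 0.75 SD. For change scores this is multiplied by √(2(1 − r)): 0.748 × 1.414 = 1.06 SD at r = 0, and 0.748 × 0.632 = 0.47 SD at r = 0.8.

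**The case against.** The best defence is that 15 per arm comes from a pilot-sizing recommendation, with the 90% and 5% describing a later main trial. Section 2.3 says the figure follows a cited paper, section 2.11 calls the study a pilot, and the Discussion looks ahead to definitive trials. This is a plausible explanation, but section 2.3 attaches the power to this trial and nothing later withdraws it. A reader might go further and conclude that the 90% belongs to a planned definitive trial. The article does not support that: it describes no such trial with a size or a power, and the cited paper is not available here. The remedy must therefore depend on the sponsor's confirmation.

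Three further points stand and limit the conclusion.

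- **The 26% is conditional.** It is the power of a two-sample comparison, and of the planned ANOVA only near r = 0.5. A reader might take 26% (or a 74% chance of missing the effect) as simply this trial's power. Without a stated correlation, that is not supported.
- **The purpose is described in two ways.** It might be inferred that the article presents an efficacy trial throughout. Section 2.11 and the end of the Discussion say otherwise.
- **The harm is softened.** Section 2.11 promises descriptive results with interval estimates, and the Discussion claims at minimum information on practicality and acceptability. An interval of about ±0.75 SD would show its own imprecision. It is therefore not certain that readers would over-interpret a null result, but the risk remains because section 2.11 also plans between-group ANOVAs.

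The attrition figures in the same section raise a separate question on which this point does not rest.

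**Conclusion.** The power statement is wrong as written. On its own inputs, 15 per arm is less than a fifth of the roughly 86 per arm needed (15/86 = 0.17), and a two-sample comparison has about 26% power rather than 90%. Under the planned ANOVA, with d on the raw SD, power runs from about 15% to 55% for correlations of 0 to 0.8, is 84% at 0.9, and reaches 90% only at about 0.92. The article neither states nor claims such a correlation.

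These figures assume 15 analysable families per arm, two-sided 5% testing and equal allocation. They do not show that the trial must be enlarged to 86 per arm: a size of 15 per arm may be reasonable for a pilot. What cannot stand is the 90% attached to it.

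**What to change.** Change the text and leave the number of families as it is.

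1. In section 2.3, remove the claim that 15 per arm gives this trial 90% power for d = 0.5.
2. If 15 per arm was taken from a pilot-sizing recommendation, the sponsor should confirm this, say so, and say which trial the 90% and 5% describe. If it was not, sample size, effect size and power must be reconciled.
3. State this trial's power for d = 0.5: about 26% for a two-sample comparison, with the range over a declared correlation for the planned ANOVA.
4. State the precision: a 95% half-width of about 0.75 SD at 15 per arm for a follow-up comparison, and about 1.06 to 0.47 SD for change scores at correlations of 0 to 0.8.
5. State that a non-significant between-group result will not be read as evidence against a medium effect.
6. Bring the efficacy wording in the Abstract, Introduction, section 2.1 and the opening of the Discussion into line with the pilot wording in section 2.11 and the end of the Discussion.

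The cost is rewriting one paragraph and making smaller wording changes elsewhere. The stated power becomes much less favourable.

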### 2.4. Recruitment

Participants will be recruited using several approaches including (a) distribution of recruitment material through early childhood education and care services and playgroups using existing networks; and (b) social marketing and targeted advertisements through online social networks, such as Facebook and online parenting forums. A study flyer, including brief information about the study and a link to the study website, will be used to distribute study information to parents through the above networks. The website provides comprehensive information about the study, including eligibility criteria, and includes a link to the baseline online survey (developed using Lime Survey). Consenting parents will need to complete the online consent form before they can proceed to the survey questions. Recruitment of participants will continue until a sample of at least 50 participants is obtained. As a thank-you for their time and participation, all participants will receive a $20 retail voucher after completing their 6-week post-intervention questionnaire.

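### Recruiting 25 per arm does not cover the stated 60% attrition: it leaves 10 per arm, not the required 15, and tolerates at most 40%

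*Protocol article*

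**What the plan says.** Section 2.3 (Sample Size) starts from the statement that "a sample size of 15 families per arm will be required". It then makes three statements about attrition.

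- The allowance and the resulting target: "Allowing for an attrition rate of 60%, 25 participants will be recruited to each arm".
- A second statement of the 60% rate, set against usual practice: "which is greater than the traditional 20% attrition rate commonly used in trials of public health interventions". The reason offered is that participants' anonymity may lower completion of the later assessment.
- The assurance: "An increase in sample size by 60% will ensure that sufficient sample size is retained".

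Section 2.4 (Recruitment) carries the figure forward: "Recruitment of participants will continue until a sample of at least 50 participants is obtained". Section 2.5 has participants "randomly allocated to the intervention or the control groups in a 1:1 ratio", so 50 in total means 25 per arm. No other section gives a different attrition rate or a further allowance.

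**The concern.** To retain a required number after losses, the required number is divided by the share that stays. Increasing it by the percentage that is lost falls short, and the gap grows with the loss. At 20% attrition the gap is trivial: 15 × 1.2 = 18 against 15/0.8 = 18.75, so 19. At 60% it is large.

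This matters because the step sets the recruitment minimum and comes with a promise that enough families will remain. Section 2.11 says that the quantitative results will be interval estimates, and the Discussion says that the study will supply parameters for later definitive trials. Both depend on how many families complete the follow-up. A reader who relies on Section 2.3 would believe that 15 per arm is protected against 60% loss, and it is not.

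**Working it through.** **Inputs, all from the protocol article.** Required per arm n = 15 (2.3). Attrition a = 0.60 (2.3, stated twice). Recruited per arm N = 25 (2.3). Minimum total 50 (2.4). Allocation 1:1 (2.5).

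**Step 1: reproduce the plan's 25.** The article shows no calculation. Two routes come close.

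- Increase by the attrition rate: 15 × (1 + 0.60) = 24, which could have been rounded up to 25. This fits the wording of the assurance.
- Divide by 0.60: 15/0.60 = 25 exactly. This treats 60% as the share retained.

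The route cannot be settled from the text, and the steps below do not depend on it.

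**Step 2: completers at the stated rate.** N × (1 − a) = 25 × 0.40 = 10 per arm, 20 in total. The shortfall is 15 − 10 = 5 per arm, and 5/15 = 33%.

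**Step 3: attrition that 25 per arm can absorb.** 1 − n/N = 1 − 15/25 = 0.40.

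**Step 4: recruitment that 60% attrition needs.** n/(1 − a) = 15/0.40 = 37.5, so 38 per arm and 76 in total. The stated minimum of 50 is 76 − 50 = 26 below this.

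**Step 5: the assurance in general.** Increasing any starting number by 60% and then losing 60% leaves 1.6 × 0.4 = 0.64 of it. The rule therefore fails whatever the required number is.

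**Step 6: chance of still reaching 15.** Assume that each family completes independently with probability 0.40. The binomial probability of at least 15 completers out of 25 is 3.4% in one arm, and 0.034² ≈ 0.1% in both arms.

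**Step 7: effect on interval width.** Assume a simple comparison of two equal arms with a common SD. The 95% half-width in SD units is t(0.975, 2n − 2) × √(2/n).

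| Analysable per arm | Half-width (SD) |
|---|---|
| 15 | 0.75 (0.748) |
| 10 | 0.94 (0.940) |

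The ratio is 0.940/0.748 ≈ 1.26, so the interval is about a quarter wider.

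**The case against.** The best defence is that 60% was a slip for 60% retention. 15/0.60 gives 25 exactly, and at 40% attrition the target is right. That may be how the figure arose, but the text does not say so. It gives 60% as attrition twice, compares it with 20% attrition, offers a reason to expect low completion, and speaks of an increase of 60%. If retention was meant, those statements are wrong and still need correcting.

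A second defence is that Section 2.11 calls this a descriptive pilot and names intention to treat. Neither repairs the arithmetic. The plan itself sets 15 per arm as required and claims to secure it. Outcomes are measured after baseline only once, at six weeks (2.1, 2.7), so analysing families as randomised does not restore missing follow-up.

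Several stronger readings are tempting, and the document does not support them.

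- *That the trial is predicted to end with 10 per arm.* Section 2.3 allows for 60% and says that anonymity may reduce completion. That is a tolerance, not a forecast.
- *That precision is worse than the plan claims.* The plan states no interval width. The half-widths above contradict nothing in it and only show the consequence.
- *That recruitment stops 26 families short.* Section 2.4 says at least 50. Only the minimum is 26 below 76.
- *That the attrition step costs the trial its stated power.* Whether 15 per arm gives the 90% power claimed for the stated effect size is a separate question about Section 2.3. This point takes the 15 as given and makes no claim about power.

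**Conclusion.** The attrition allowance in Section 2.3 is wrong as written. A requirement of 15 per arm, recruitment of 25 per arm and 60% attrition are mutually inconsistent, and the assurance that enough families will be retained is false. At the stated rate 10 per arm remain. The stated recruitment protects 15 only up to 40% attrition, and 60% would need 38 per arm.

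This rests only on the plan's own figures and on the ordinary meaning of attrition as the share lost. The route by which 25 was reached is uncertain and does not affect the result. The rise in half-width from 0.75 to 0.94 SD also assumes a plain two-group comparison with equal SDs and equal numbers in each arm.

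**What to change.** Keep 25 per arm and make the three attrition statements in Section 2.3 agree, in one of two ways.

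1. **Restate the tolerance.** Say that 25 per arm retains 15 only if attrition is no more than 40%. Change both statements of 60% and delete the assurance. Changing only one of the 60% statements would leave a new contradiction. The comparison with the usual 20% can stay, since 40% also exceeds it. Because the section gives a reason for a large allowance, the authors should say why 40% is considered adequate.
2. **Keep 60% as the allowance.** State that about 10 per arm (20 in total) would then be analysable, give the expected precision for that number, and delete the assurance. The text should acknowledge that 15 per arm is not secured at that rate.

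Both are changes of wording in one section. They cost no additional families and leave the minimum of 50 in Section 2.4 as it is. The price is a less favourable statement of what the trial can absorb.

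Recruiting 38 per arm is the direct arithmetic correction if both the 15 and the 60% are to stand. It would raise the minimum by 26 families, and the restatement does not need it.
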